**Sample size:**

The study will recruit 300 participants (150 for each arm).

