**Inclusion/Exclusion criteria**:

Inclusion criteria:

- Patients aged 18 to 65, inclusive, who present to the primary care centre seeking treatment for anxiety, depressive or somatic symptoms.

- Scores above the predetermined cut-off points on the GAD-7 (>= 10), the PHQ-9 (>= 10) or the PHQ-15 (>=10 plus a score of 2 in three or more somatic symptoms).

- Agreement to participate in the study, with written informed consent.

Exclusion criteria:

- Major depressive disorder (PHQ-9> 24) and/or severe disability (SDS > 25) will be interviewed by a clinician for the presence of any severe mental disorder, including autism spectrum disorders, bipolar disorder, schizophrenia, anorexia nervosa, substance dependence, personality disorder.

- Presence of severe or recent suicide attempts

- Presence of intellectual disability (IQ < 70).

- Be receiving psychological treatment or any type of specialized care related to mental health.

- Insufficient Spanish language skills

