**Outcome Measures**

Primary Outcome Measures:

- Change in cost-effectiveness data [Time Frame: Baseline, immediately after the intervention, and 12-month follow-up]

Cost-effectiveness results will be calculated by the ICER, defined as the difference in mean costs between interventions divided by the difference in their effectiveness according to the symptom questionnaires’ mean scores.

The healthcare data collected will be used for cost calculations. To calculate healthcare-related costs, an ad hoc questionnaire will be used to collect emotional disorder-related healthcare data (public and private healthcare consultations, accidents, medical tests, and sick leaves in the past 3 months; psychotropic drugs or other medication, and their posology).

- Change in cost-utility data [Time Frame: Baseline, immediately after the intervention, and 12-month follow-up]

Cost-utility will be measured through the healthcare data collected above and the European Quality of Life Scale (EuroQoL, EQ) [71], calculating the QALYS and the ICURs, defined as the difference in mean cost divided by the difference in mean QALYs. The Spanish version of the 5-domain, 5-level EuroQol (EQ-5D-5L) [72,73] will be used to assess health status in five dimensions (mobility, self-care, daily activities, pain/unease, and anxiety/depression) with five levels of severity (no problems, slight problems, moderate problems, severe problems, and either extreme problems or unable to perform activity). The scores obtained in the different dimensions can be combined to create a 5-digit code describing the patient's state of health, being able to stablish up to 3125 different combinations, and therefore, different possible health states. This system was converted into a utility score using the value set for Spain from the EQ-5D-5L Crosswalk Index Value downloaded from the EuroQol website (<https://euroqol.org/euroqol/>).

Secondary Outcome Measures:

- Change in depressive symptoms: Patient Health Questionnaire - 9 item (PHQ-9) [Time Frame: Baseline, immediately after the intervention, and 12-month follow-up]

The PHQ-9 [54] is the depression module of the PHQ [74, 75] that scores the 9 DSM-IV depression criteria in the last two weeks. Is a nine item, self-report scale that ranges from 0 to 27 (higher scores means a worse outcome).

- Change in anxiety symptoms: Generalized Anxiety Disorder - 7 item (GAD-7) [Time Frame: Baseline, immediately after the intervention, and 12-month follow-up]

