**Statistical analysis**

Both parallel groups will be tested for equivalence on pre-treatment measures. In the efficacy analysis, 2x2 (group x treatment) intergroup-intragroup ANOVAs will be carried out on the dependent measures: 1) symptoms of anxiety, depression and somatisation; 2) cognitive-emotional factors associated with symptoms; 3) occupational, family and social dysfunction; 4) quality of life; 5) satisfaction with care received; 6) cost-effectiveness analysis (e.g., frequentation, drug consumption). The effect size of both groups on the different dependent variables will be calculated, as well as their precision (95% confidence intervals), taking into account the number of sessions received. The percentages of patients in both groups who have decreased their clinical symptom scores by 50% and by one standard deviation, as well as the percentages of probable cases with mental disorders (anxiety, depressive and somatoform) before and after treatment, according to the cut-off points and decision rules for diagnosis, will also be calculated. The primary analyses will follow the "intention-to-treat" principle, so that all individuals who have entered the study will be considered in their corresponding group, even if they have not complied with their protocol. This will allow the objective of randomisation to be maintained until the end of the study, i.e. to reduce the likelihood of biasing the results.

The cost-effectiveness analysis will be carried out by calculating the increase in cost-effectiveness ratios, defined as the difference between the mean costs divided by the increase in effectiveness between the different therapeutic alternatives compared (ICER).

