**APPLICABILITY AND USEFULNESS OF THE RESULTS AND ABILITY TO BE PROTECTED AND TRANSFERRED TO THE MARKET**

The planned clinical trial will provide clear evidence that, compared to treatment through relaxation, the incorporation of a group treatment for mental disorders commonly treated in Health Centres helps to reduce anxious, depressive and somatic symptomatology, as well as a reduction in the costs (direct and indirect) associated with anxiety, mood and somatoform disorders (Main hypothesis). PsicAP-Costs2 allows an immediate transfer of the results to the clinical context by providing the first experience in our context of a manualised transdiagnostic group treatment of short duration (7 sessions), which makes it easily applicable and generalizable to health centres in Cantabria and the rest of the NHS. The expected economic benefit in the reduction of psychopharmacological treatment costs and through the reduction of expenditure on sick leave and loss of productivity, which is a priority objective of the SCS in the management of TI associated with common mental disorders (Mental Health Plan of Cantabria 2015-2019), should make the dissemination among health professionals of this type of protocolised treatment, low cost and short duration, easily integrated into the routine care offered in Health Centres, profitable.

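### Efficacy would be better estimated as a baseline-adjusted TD-CBT minus PMR difference with its 95% CI than by a raw-change 2x2 ANOVA with effect sizes worded per arm

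*Protocol*

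**What the plan says.** The Statistical analysis section of the protocol gives the efficacy model as "2x2 (group x treatment) intergroup-intragroup ANOVAs will be carried out on the dependent measures". The measures include symptoms, cognitive-emotional factors, dysfunction, quality of life and satisfaction. The section does not say which of the model's terms gives the efficacy result. It continues: "The effect size of both groups on the different dependent variables will be calculated, as well as their precision (95% confidence intervals". The responder summaries in the next sentence are worded in the same way: "The percentages of patients in both groups who have decreased their clinical symptom scores by 50% and by one standard deviation".

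The question itself is comparative. The applicability section words its main hypothesis as follows: "compared to treatment through relaxation, the incorporation of a group treatment for mental disorders commonly treated in Health Centres helps to reduce anxious, depressive". The same sentence also covers somatic symptoms and costs. The Primary purpose section also sets TD-CBT against relaxation. For the economic outcome, the Outcome Measures section does write out a contrast between arms; the ICER is "defined as the difference in mean costs between interventions divided by the difference in their effectiveness according to the symptom questionnaires’ mean scores".

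**The concern.** The plural wording of the effect-size sentence, and the parallel wording of the responder sentence, point to one value per arm. A before-after interval for one arm describes how much those patients changed. It does not describe how much more they changed than patients in the other arm. Both arms receive seven group sessions and continue usual GP care, and patients enter because a score is at or above a cut-off ("Scores above the predetermined cut-off points on the GAD-7 (>= 10), the PHQ-9 (>= 10) or the PHQ-15"). Some improvement in both arms is therefore plausible whatever TD-CBT adds.

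The model does contain a test of the comparison, but in its raw-change form. For most measures the baseline value is already collected, and a raw-change comparison uses it less well than adjustment does. What is at stake is precision on the clinical outcomes, and whether the reported interval answers the trial's question.

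**Working it through.** **Inputs.** From the Sample size section: "The study will recruit 300 participants (150 for each arm". The protocol gives no alpha, power, effect size, SD, before-after correlation or dropout rate, so the figure of 300 cannot be reproduced. For orientation, at two-sided 0.05 an unadjusted comparison with 150 per arm detects (1.960 + 0.842) × √(2/150) = 0.32 SD with 80% power, and 0.37 SD with 90%.

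**Assumptions for the rest.** SD 1 at both visits; equal baselines by randomisation; true post-treatment difference d = 0.3 SD (0.2 and 0.4 also shown); before-after correlation r = 0.3, 0.5 or 0.7; two-sided 0.05; no dropout; independent patients, so clustering by therapy group is ignored.

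**What each ANOVA term tests.**
- Time: mean change pooled over the arms. It says nothing about TD-CBT against PMR.
- Group: the arm difference in the average of before and after. Its expected value is d/2, because baselines are equal.
- Interaction: the arm difference in change. Its expected value is d, and it is equivalent to a two-sample t-test on raw change.

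**Precision of the two candidate contrasts.** Each standard error is the SD below times √(2/150) = 0.1155.
- Interaction (raw change): SD = √(2(1−r)).
- Baseline-adjusted difference: SD = √(1−r²).

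The variance ratio, adjusted to raw change, is (1−r²)/(2(1−r)) = (1+r)/2, that is 0.65, 0.75 and 0.85. Adjustment is more precise at every r below 1.

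**Power** = Φ(d/SE − 1.96). For r = 0.5 and d = 0.3:
- Interaction: SD 1, SE 0.1155, 0.3/0.1155 = 2.598, Φ(0.638) = 73.8%.
- Adjusted: SD 0.866, SE 0.100, 0.3/0.100 = 3.00, Φ(1.04) = 85.1%.

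| d | r | Interaction | Baseline-adjusted | Gain (points) |
|---|---|---|---|---|
| 0.2 | 0.3 | 31.0% | 44.3% | 13.3 |
| 0.2 | 0.5 | 41.0% | 51.6% | 10.6 |
| 0.2 | 0.7 | 60.9% | 67.9% | 7.0 |
| 0.3 | 0.3 | 59.3% | 77.7% | 18.4 |
| 0.3 | 0.5 | 73.8% | 85.1% | 11.3 |
| 0.3 | 0.7 | 91.8% | 95.3% | 3.5 |
| 0.4 | 0.3 | 83.3% | 95.3% | 12.0 |
| 0.4 | 0.5 | 93.4% | 97.9% | 4.5 |
| 0.4 | 0.7 | 99.4% | 99.8% | 0.4 |

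**What a per-arm interval estimates.** Suppose both arms improve by 0.5 SD, with no difference between them, and r = 0.5. Each arm's change has SE √(1/150) = 0.0816, so its expected 95% interval is 0.5 ± 0.16, or 0.34 to 0.66. The interval for the difference in change is 0 ± 1.96 × 0.1155, or −0.23 to 0.23. In 6,000 simulated trials of this case both per-arm intervals excluded zero in 100%, and the interaction rejected in 4.8%. Each per-arm interval is correct for its own question, but that is not the question of TD-CBT against PMR.

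**The case against.** The strongest reply is that the right test is already planned. The notation in "2x2 (group x treatment) intergroup-intragroup ANOVAs will be carried out on the dependent measures" can be read as the interaction, which under randomisation is valid and unbiased, and naming the deciding term can be left to a statistical analysis plan. This stands. The point is therefore about a more efficient estimate and a clearer interval, not about a missing or invalid test.

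Second, the effect-size sentence is loosely worded, and an effect size between arms cannot be excluded. Describing each arm's change with its precision is also legitimate beside a test between arms. Both stand. The per-arm reading is likely, not certain.

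Third, differences between arms are defined elsewhere. The ICER denominator is a difference in symptom scores and the ICUR denominator a difference in QALYs, and the Abstract plans bootstrap sampling for uncertainty. So it would be wrong to say that the protocol has no contrast between arms for symptoms or quality of life. The bootstrap sentence does not name those differences, however, and the efficacy paragraph does not carry them over.

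A reader might go further and infer that a per-arm interval excluding zero would be reported as efficacy, or that the group term would be taken as the test between arms. At d = 0.3 the group term has power of only 36%, 32% and 29% at r = 0.3, 0.5 and 0.7. No section says that either would be used to claim superiority, so these readings are not supported. Nor is 0.3 SD a design value of the trial.

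**Conclusion.** The point holds as an improvement in efficiency and clarity. The planned interaction is a valid test of TD-CBT against PMR, but it compares raw changes, and the planned intervals, as most naturally read, do not estimate the difference between arms. Adjusting for baseline gains about 18, 11 and 4 points of power at d = 0.3 and r = 0.3, 0.5 and 0.7. Over d = 0.2 to 0.4 the gain runs from 0.4 to 18.4 points, and it is small where the correlation is high and the effect large. Only the 150 per arm comes from the protocol. Dropout or clustering by therapy group would lower all the power figures.

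The weight is moderate. The Outcome Measures section lists symptoms, functioning and satisfaction as secondary, and the primary ICER and ICUR are contrasts between arms by definition. Symptom reduction against relaxation is nevertheless part of the main hypothesis as the applicability section words it, and symptom scores supply the effectiveness part of the ICER.

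**What to change.** In the Statistical analysis section, state that the efficacy result for each measure is the TD-CBT minus PMR difference at each follow-up visit (post-treatment and 12 months), adjusted for the baseline value of that measure, with its 95% CI. Add a standardised effect size by dividing that difference by the pooled baseline SD. Satisfaction is collected only after treatment, so use the unadjusted difference there, standardised by the pooled SD at that visit. Keep each arm's before-after change as description only.

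The cost is a change of wording. The baseline values are already in the assessment schedule, and no visit, questionnaire or patient is added. The headline effect sizes will probably be smaller than before-after values for a single arm, because they no longer include improvement common to both arms.

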**Abstract:**

The aim of this study is to test the cost-effectiveness and cost-utility of adding a transdiagnostic group cognitive-behavioural therapy (TD-CBT) to treatment as usual (TAU) for emotional disorders in primary care . A single-blind randomized controlled clinical trial will be conducted to compare the TD-CBT group therapy plus TAU to progressive muscle relaxation (PMR) group plus TAU in individuals, aged 18 to 65, with emotional disorders in four primary care centres located in Cantabria, Spain. The study will take a societal perspective. Psychological assessments will be carried out at baseline, post-treatment, and 12-months follow-up. The assessments will include measures of clinical symptoms (anxiety, depression, and/or somatic), dysfunction, cognitive-emotional factors (ruminative processes, pathological concern, attentional and interpretative biases, emotion regulation strategies and meta-cognitive beliefs), and satisfaction with the treatment received. Data on health service use, including medication and days of absence from work, will be collected from electronic medical records. The primary outcomes are the incremental cost-effectiveness ratios (ICER) based on the difference in mean costs and effectiveness between interventions and incremental cost-utility ratios (ICURs) based on health-related quality of life at post-treatment and 12-month follow-up. Secondary outcome measures include clinical symptoms, quality of life, functioning and treatment satisfaction. Bootstrap sampling will be used to assess the uncertainty of the results. Secondary moderation and mediation analyses will also be conducted. In addition, in sessions' number 1, 4 and 7 of both treatment arms, two questionnaires will be administered that collect therapeutic alliance and group satisfaction. The main study hypothesis is that adding TD-CBT to TAU in primary care will be more cost-effective than TAU plus PMR. In addition, these gains will be maintained in the 12-month follow-up. If it is successful, the dissemination of cost-effective treatment can help to overcome problems in accessing psychological treatment for emotional disorders in the context of an increasing demand for mental healthcare in primary care.

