**METHODOLOGY**

**Description of the type of trial**

A prospective, single-blind, randomized controlled trial will be carried out in two PC health centers in Cantabria (Camargo Costa and Camargo Interior). Patients attending their PC center with possible common mental disorders (related to anxiety, depression or somatization) not susceptible to be referred to specialized care according to the criteria of their referring physician in the health center, will be invited to participate in the study, as well as to sign the informed consent form. Those who accept will be assessed before being assigned to groups, so the assessors will be blinded to treatment assignment at all times. Cases who have completed testing will be randomly assigned to the two treatment conditions: (i) control group with treatment using Bernstein and Borkovec's progressive muscle relaxation techniques together with treatment as usual by their GP; or (ii) experimental group with manualized group treatment based on CBT plus treatment as usual by their GP.

Patients assigned to both groups will receive 7 sessions of 1.5 hours duration, in subgroups of approximately 10-12 persons, spread over 12 weeks, with a higher temporal frequency at the beginning of the treatment (one session per week) and progressive extension of the time interval between sessions as the treatment progresses.

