**Name of each arm:**

| Arms | Assigned Interventions |
| --- | --- |
| Experimental: transdiagnostic cognitive-behavioural therapy (TD-CBT)  Transdiagnostic group cognitive-behavioural therapy: The psychological interventions will be manualized. Patients assigned to the experimental group will receive 7 sessions (1.5 hr/session) in groups of approximately 8-10 individuals over a 12-week period. | Behavioural: Transdiagnostic cognitive-behavioural therapy (TD-CBT). |
| Active Comparator: Relaxation therapy  The control group will receive a PMR group intervention, based on the Bernstein and Borkoveck procedure. Patients will receive 7 sessions (1.5 hr/session) in groups of 8-10 individuals over a 12-week period. | Bernstein and Borkovec progressive muscle relaxation (PMR) |

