**The transdiagnostic, group psychological treatment of the experimental group.**

The psychological intervention offered (which will be applied by psychologists) will be protocolised (with a Therapist's Manual) and described in a document addressed to the patient. The patients assigned to the experimental group will receive 7 sessions of 1.5 hours duration in groups of approximately 10 people, spread over 24 weeks, with a greater temporal frequency at the beginning of the treatment (one session per week) and a progressive extension of the time interval between sessions as the treatment progresses. The treatment protocol will be adjusted to the following contents:

Sessions 1: This group will start the psychological treatment with psychoeducational training, in order to provide participants with concrete information (oral and written), as well as information resources (e.g., books, website), on stress, emotions, anxiety, anger, depression, the role of cognitive processes and biases on emotion, emotional learning, emotion regulation, relationships between emotion and behaviour, etc., trying to adapt the contents to the needs of the participants. In all sessions, patients will be motivated to take an active role in the treatment and to carry out the corresponding daily homework.

Session 2: Relaxation techniques will be introduced, with a mixture of Bernstein and Borkovec's progressive muscle relaxation training, abdominal breathing and imagery training. The principles of these exercises, the intended objectives and how to perform the training will be explained. In addition, patients will be asked to practice these exercises daily at home with an audio recording that will be provided, lasting approximately 30 minutes. In order to develop motivation and the habit of practising this task, patients will be asked to make a graphic self-recording of their daily evaluation of the degree of relaxation experienced after the practice, throughout the 24 weeks of the intervention.

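### Both arms are treated in therapy groups of about 8 to 12, but the planned 2x2 ANOVAs and their 95% confidence intervals have no therapy-group term, so standard errors are too small if outcomes correlate within groups

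*Protocol*

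**What the plan says.** The unit of randomisation is the patient (Description of the type of trial): "Cases who have completed testing will be randomly assigned to the two treatment conditions". The Sample size section is a single sentence, "The study will recruit 300 participants (150 for each arm", with no allowance for clustering.

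Treatment in both arms is then given in therapy groups. The stated sizes differ by section:

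- Description of the type of trial, both arms: "in subgroups of approximately 10-12 persons".
- Name of each arm: "in groups of approximately 8-10 individuals over a 12-week period" (experimental) and "in groups of 8-10 individuals over a 12-week period" (control).
- The section on the experimental treatment: "7 sessions of 1.5 hours duration in groups of approximately 10 people". The section on relaxation treatment gives the same size.

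The Statistical analysis section prescribes 2x2 between-within ANOVAs for six families of measures. They include symptoms, quality of life and cost-related inputs such as service use and drug consumption. On precision it says: "The effect size of both groups on the different dependent variables will be calculated, as well as their precision (95% confidence intervals". The bootstrap appears only in the Abstract: "Bootstrap sampling will be used to assess the uncertainty of the results".

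**The concern.** Members of a therapy group attend the same seven sessions and work together on one another's recent experiences. The protocol itself treats the group as a possible influence, since it measures alliance to the group at sessions 1, 4 and 7. Patients who were independent at randomisation may therefore have correlated outcomes afterwards.

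A 2x2 ANOVA with arm as the between-patient factor and time as the within-patient factor has no place for this correlation. With two levels per factor, neither factor can stand for some 30 therapy groups. The model allows for repeated measures on a patient but treats different patients as independent.

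At stake is the validity of the efficacy comparisons. Intervals would be too narrow, and a difference between arms would be declared by chance more often than the nominal rate. The error runs in one direction. Because this model is written into the protocol, an analysis plan that followed it faithfully would carry the problem forward.

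**Working it through.** **Inputs from the protocol.** N = 300, 150 per arm; therapy-group size m from 8 to 12, with 10 as the central value; 95% intervals.

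**Assumptions.** The ICC is not given, so a range of 0 to 0.10 is used. No significance level is stated either; two-sided 5% is inferred from the 95% intervals. Groups are taken as equal in size and fully attended, and the ICC is that of the quantity compared, which in an arm-by-time ANOVA is the change from baseline.

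**A figure to reproduce.** There is none. The 300 cannot be re-derived, because no effect size, standard deviation, power or dropout rate accompanies it.

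**Formulas.**

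- Groups per arm = 150/10 = 15.
- Design effect DE = 1 + (m − 1) × ICC.
- Correct standard error / planned standard error = √DE.
- Effective sample = 300/DE.
- Real error of a nominal 5% test = 2 × [1 − Φ(1.96/√DE)].

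**Results for m = 10.**

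| ICC (assumed) | DE | √DE | Effective sample | Real error |
|---|---|---|---|---|
| 0 | 1.00 | 1.00 | 300 | 5.0% |
| 0.01 | 1 + 9 × 0.01 = 1.09 | 1.04 | 275 | about 6% |
| 0.02 | 1 + 9 × 0.02 = 1.18 | 1.09 | 254 | 7.1% |
| 0.05 | 1 + 9 × 0.05 = 1.45 | 1.20 | 207 | 10.4% |
| 0.10 | 1 + 9 × 0.10 = 1.90 | 1.38 | 158 | 15.5% |

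**Sensitivity to the stated group sizes, at ICC 0.05.** For m = 8, DE = 1.35, √DE = 1.16 and the error is 9.2%. For m = 12, DE = 1.55, √DE = 1.25 and the error is 11.5%.

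**Check by simulation.** Over 20,000 simulated trials with 15 groups of 10 per arm and no true difference, a test that ignored the groups rejected in 4.7%, 6.9%, 10.4% and 15.8% of trials at ICC 0, 0.02, 0.05 and 0.10. A test on therapy-group means stayed between 4.7% and 5.2%.

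**Which bootstrap would work.** Let K = 15 groups per arm, m = 10, and total variance 1. The true variance of an arm mean is [ICC + (1 − ICC)/m]/K.

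- Resampling groups and then patients within them gives, on average, {(14/15) × [ICC + (1 − ICC)/10] + (9/10) × (1 − ICC)/10}/15. The second term counts within-group variance again. At ICC 0 the ratio to the truth is (0.0933 + 0.0900)/0.1000 = 1.83, so the standard error is √1.83 = 1.35 times too large. At ICC 0.05 it is (0.1353 + 0.0855)/0.1450 = 1.52, a factor of 1.23.
- Resampling whole groups only gives √(14/15) = 0.97 at any ICC, about 3% too small.

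**The case against.** The strongest reply is that the documents contain no ICC. At 0.01 the standard error is off by only 4%, and at zero nothing is wrong. This stands, and it is why the conclusion is conditional. It does not rescue the ANOVA, because nothing in the protocol supports an ICC of zero.

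The size is also simplified. The intention-to-treat analysis keeps patients who do not comply, which dilutes shared exposure. The ICC of change may be lower or higher than that of a single score, and it may differ at 12 months, long after the groups have ended. A shared therapist is not stated: the protocol says only that psychologists deliver the treatments. Shared sessions are explicit and are enough for the argument.

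A reader might infer that the bootstrap also treats patients as independent, so that the intervals for the primary cost-effectiveness and cost-utility ratios are too narrow. The documents do not support this. The one sentence on the bootstrap names no resampling unit, and that detail may properly be settled in an analysis plan that is not shown. The documented defect therefore lies in the ANOVAs and their intervals. These cover mainly secondary and mechanistic measures, together with the symptom, quality-of-life and cost components that feed the ratios, but not the ratios themselves.

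**Conclusion.** The point holds for the 2x2 ANOVAs and their 95% confidence intervals, conditionally on correlation within therapy groups. With 10 per group, an ICC of 0.01 to 0.10 makes the planned standard errors too small by a factor of 1.04 to 1.38 and moves a nominal 5% test to a real error of about 6% to 16%. The ICC range is an assumption, as are equal, fully attended groups and a two-sided 5% level.

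The text supports neither an unconditional claim that the standard errors are too small nor any claim that the uncertainty around the primary ratios is understated. For the bootstrap, the only conclusion is that its resampling unit remains to be set.

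**What to change.** 1. Record a therapy-group identifier for every randomised patient. Patients who never attend carry the group to which they were scheduled, so that the intention-to-treat set stays complete.
2. Replace the 2x2 ANOVAs with mixed models that have a random intercept for therapy group in both arms and a small-sample correction, since there are only about 15 groups per arm. Kenward-Roger is one choice; cluster-robust variance with a small-sample correction is another. The random effect must act on the treatment contrast: model the post-treatment outcome with baseline as a covariate where one exists. An intercept common to baseline and follow-up cancels out of the change and corrects nothing.
3. When the bootstrap for the cost-effectiveness and cost-utility ratios is specified, resample whole therapy groups within arm, keeping each patient's costs and effects together. Do not resample groups and then patients.
4. Reconcile the group sizes given in the different sections, because they set the design effect.

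The cost is one variable in the dataset and some analysis code. The downside is wider intervals if the ICC is above zero: about 20% wider at 0.05 with groups of 10.

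### The only effect sizes with confidence intervals that the protocol describes are conditioned on sessions attended, so as between-arm estimates they would not be intention-to-treat

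*Protocol*

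**What the plan says.** All of this is in the protocol's Statistical analysis section unless noted.

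- Efficacy test: "2x2 (group x treatment) intergroup-intragroup ANOVAs will be carried out on the dependent measures". Six groups of measures follow: symptoms, cognitive-emotional factors, dysfunction, quality of life, satisfaction and a cost item, "6) cost-effectiveness analysis (e.g., frequentation, drug consumption"). No session term appears.
- Effect sizes: these, with 95% intervals, are to be reported for the two groups on those measures, "taking into account the number of sessions received". This is the only place where effect sizes with intervals are described.
- Analysis principle: "The primary analyses will follow the 'intention-to-treat' principle, so that all individuals who have entered the study will be considered in their corresponding group". The sentence goes on to say that non-compliers are kept as well.
- Primary outcomes (Abstract): "The primary outcomes are the incremental cost-effectiveness ratios (ICER) based on the difference in mean costs and effectiveness between interventions", together with the cost-utility ratios. Under Outcome Measures the cost-effectiveness ratio is "defined as the difference in mean costs between interventions divided by the difference in their effectiveness according to the symptom questionnaires", again with no session term. Symptoms, functioning and satisfaction are secondary.
- Both arms are offered seven sessions, and 300 patients are to be recruited, 150 per arm.

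**The concern.** The number of sessions a patient receives is settled after allocation. It can depend on what the arm asks of the patient: the experimental arm adds cognitive restructuring, exposure and homework, while the control arm is relaxation. It can also depend on how well the patient was going to do anyway. Patients with the same attendance in the two arms need not be comparable, so conditioning an arm contrast on attendance gives up the protection of randomisation for that estimate.

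Missing sessions is the most obvious form of non-compliance in a seven-session therapy. The section sets it aside for the primary analyses and then brings it into the effect estimates, without saying how the two fit together. Someone following the text could publish attendance-conditioned figures as the trial's effect sizes, and could choose the method after attendance is known.

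**Working it through.** **1. No planned figure to reproduce.** The sentence states no number, and the documents give no attendance rate, no attendance gap and no link between attendance and prognosis. Everything below on size is illustrative.

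**2. Mechanism.** Suppose the clause means sessions enter as a covariate. In a linear model of outcome on arm and sessions,

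adjusted effect = by-allocation effect − γ × (mean sessions TD-CBT − mean sessions PMR),

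where γ is the within-arm slope of outcome on sessions. If sessions have no causal effect of their own, the second term is pure bias. It vanishes when mean attendance is equal or when γ is zero. Its sign depends on which arm attends more and on the sign of γ.

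**3. Simulation.** The 150 per arm comes from the protocol. Assumed: outcome SD 1, higher = better; a latent prognosis correlated 0.5 with outcome; sessions rounded and limited to 0–7; attendance correlated 0, 0.3 or 0.6 with prognosis; sessions causally inert; 4,000 replicates. True effect 0.30:

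| Mean sessions PMR / TD-CBT | Attendance–prognosis correlation | By allocation | Adjusted for sessions |
|---|---|---|---|
| 4.89 / 4.88 | 0.6 | 0.301 | 0.302 |
| 4.89 / 5.68 | 0 | 0.300 | 0.301 |
| 4.88 / 5.30 | 0.3 | 0.301 | 0.263 |
| 4.88 / 5.31 | 0.6 | 0.303 | 0.226 |
| 4.89 / 5.68 | 0.3 | 0.301 | 0.228 |
| 4.89 / 5.68 | 0.6 | 0.302 | 0.154 |
| 4.89 / 6.01 | 0.3 | 0.298 | 0.190 |
| 4.89 / 6.01 | 0.6 | 0.302 | 0.088 |

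With a true effect of zero, the by-allocation test rejected in 4.6% to 5.5% of trials. The adjusted test rejected in 9.2% and 26.4% at a gap of 5.68 − 4.89 = 0.79 sessions (correlation 0.3 and 0.6), and in up to 43.0% at the largest gap.

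**4. Per session.** From the rows with a gap of 0.79:

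- correlation 0.3: (0.301 − 0.228) / 0.79 = 0.09 SD per session;
- correlation 0.6: (0.302 − 0.154) / 0.79 = 0.19 SD per session.

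**5. Both directions.** A second simulation used a true effect of −0.30 (negative = improvement), 150 per arm, about 5 of 7 sessions attended, a prognostic factor correlated 0.5 with outcome that also drives attendance, inert sessions, and 1,500 trials per scenario.

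- Equal attendance: −0.295 to −0.298.
- TD-CBT one session more: −0.184 to −0.207, a loss of 0.09 to 0.12.
- TD-CBT one session fewer: −0.403 to −0.422, an inflation of 0.10 to 0.12.
- Half a session either way: a shift of about 0.05 to 0.06.

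**6. Scale.** With 150 per arm the standard error of a standardised difference is about √(2/150) = 0.115, so the 95% half-width is 1.96 × 0.115 = 0.23. A shift of 0.1 to 0.2 is roughly 0.4 to 0.9 of that half-width.

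**7. Per-arm reading.** The wording may instead mean a pre–post effect within each arm. The simulations then do not apply, because there is no arm contrast to adjust. The sentence still would not supply the TD-CBT versus relaxation effect size with its interval, which is the comparison named in the protocol's Primary purpose.

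**The case against.** A reader might infer that the clause undoes the intention-to-treat comparison, or that the section flatly contradicts itself. The text supports neither. The principle is stated for the primary analyses, the primary outcomes are the cost-effectiveness and cost-utility ratios, and neither those nor the ANOVAs carry a session term. A different estimand reported beside an intention-to-treat result is not in itself a contradiction.

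A reader might also infer that the reported effects would be biased. That goes too far. Both arms are offered the same seven sessions, and equal attendance, or attendance unrelated to prognosis, leaves no bias. The direction cannot be predicted either: if early improvers stop coming, the sign of γ changes and so does the bias.

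The clause is also loose. It could mean a covariate, a dose-response description, or within-arm effects shown by attendance, and such method detail is commonly left to an analysis plan. This limits what can be said about size and lowers the severity. It does not remove the point, because the problem lies in what the protocol states. The only effect sizes it describes carry the qualifier, and nothing marks them as supplementary. Each plausible reading gives either an estimate that is not intention-to-treat or one that does not compare the arms.

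**Conclusion.** The point holds as a moderate issue about how effect sizes, mostly on secondary measures, are specified. Read as a between-arm estimate, the clause conditions on a post-randomisation variable and departs from the section's own principle. The possible bias is about 0.1 to 0.2 SD for a gap of about one session. That range rests on covariate adjustment, inert sessions and an assumed attendance–prognosis correlation of about 0.3 to 0.6, none of which comes from the documents. The plan's intention-to-treat primary analyses, ANOVAs and cost ratios stand as written.

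**What to change.** Replace the clause with a sentence to this effect: between-arm standardised effect sizes with 95% confidence intervals will be estimated by allocated group in all randomised patients, regardless of attendance, adjusted, if at all, only for baseline covariates. Add that attendance will be described by arm, and that any analysis relating sessions to outcome is supplementary and exploratory, with its method named. If within-arm pre–post effects are also wanted, present them as descriptive.

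The cost is a short change of wording. No data collection, sample size or primary analysis changes.
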